## Abstract

**Background:**

Sexual violence against adolescents is prevalent worldwide and results in significant physical and mental injuries as well as loss of economic and personal potential. Urban informal settlements such as those around Nairobi, Kenya have been shown to have especially high incidences of violence. Research has shown that empowerment interventions for female adolescents can reduce sexual assault. However, these interventions have had limited testing in urban informal settlements, with young adolescents, or in coordination with complementary programs for male adolescents.

**Methods/design:**

This study was a two-arm, parallel, cluster-randomized trial testing a combination of a previously-tested girls’ intervention, IMPower, and a newly revised boys’ intervention, Source of Strength. Clusters were defined as schools within the informal settlements; participants were adolescent girls and boys in class 6, generally between the ages of 10–14 at baseline. Data collection began in January 2016 and continued through December 2018. The primary outcome was the change in incidence of self-reported sexual assault among girls from baseline, compared to a life skills standard of care intervention. Secondary outcomes included experiences of physical and emotional violence, as well as determining the effects of the intervention on self-efficacy, self-esteem, and gender attitudes and beliefs, and how those effects led to changes in experience of sexual assault. For the primary outcome and several of the secondary outcomes, we used an intention to treat estimand.

**Discussion:**

This was the first randomized controlled trial with longitudinal follow-up of an empowerment self-defense approach to violence prevention for adolescents in informal settlements. The large size and rigorous design supported analysis to understand multiple subgroup experiences in the hypothesized reduction in sexual assault. The study was also unique in its focus on young (10–14 years of age) adolescents and in engaging both boys and girls in separate but coordinated curriculums. The focus on a highly vulnerable and understudied population will make it a significant contribution to the literature on violence prevention.

**Trial registration:**

Clinical Trials.gov #NCT02771132. Version 3.1 registered May 2017, first participant enrolled January 2017. Retrospectively registered.

## Background

An estimated 120 million girls worldwide – 1 in 10 – are raped or sexually assaulted by the age of 20 years [1]. In sub-Saharan Africa, 16 to 59% of adult women report having ever been sexually assaulted, with many assaults occurring during adolescence or childhood [2]. The 2010 Kenya Violence Against Children Survey (VACS) showed that 11% of girls and 4% of boys aged 13–17 experienced some type of sexual violence in the 12 months prior to the survey, and 3 out of 10 girls and 2 out of 10 boys reported at least one episode of sexual violence before the age of 18 [3]. Adolescents living in the informal settlements, or slum communities, of Nairobi, Kenya also report high rates of sexual assault, between 8 and 25% annually [4–6], depending on age. Furthermore, cross-sectional data from nine countries confirm that adolescent girls and young women are at higher risk of intimate partner violence (IPV), which may include sexual assault, than older women [7]. Sexual assault of young people results in a wide range of negative health and social outcomes, including physical injury or disability, unplanned pregnancies, psychological trauma, and school drop-out [8–13].

### Knowledge gaps

To-date, most sexual assault prevention interventions have been evaluated in high-income countries [14]. Limited research has been conducted about sexual assault either among adolescents or in informal settlements, and very minimal research is available at the intersection of young people in informal settlements, despite them being a large, high-risk, and growing population. Informal settlements are an important setting to study, as they are growing quickly worldwide, and have high rates of violence, infectious disease, and other threats to human health and well-being [15].

A few interventions have shown promise in low- and lower-to-middle income countries (LMIC), although generally with older populations or in dis-similar settings. The most relevant of these is the combined Stepping Stones and Creating Futures intervention, which was implemented in informal settlements around Durban, South Africa in 2014 [16, 17]. Although the study population consisted of older adolescents and young adults (18–30 years of age), the environmental characteristics of the settlements are similar to the setting where we plan to conduct this trial: high poverty rates, inadequate access to clean water and sanitation, poor quality of housing, and overcrowding. That preliminary study found improvements in gender attitudes and mental health as well as a decrease in controlling behaviors by men as a result of the intervention. A large, randomized controlled trial of this is currently underway in similar communities in South Africa, the findings of which will be important to compare to results from the study described here.

A larger and more rigorous trial was the 2014 evaluation of SASA!, which showed that community mobilization improved gender norms and reduced intimate partner violence (IPV) incidence and acceptability among both adult women and men in in Kampala, Uganda [18]. The SHARE study, also in Rakai, Uganda, included adolescents from 15 years of age (although it also included adults up to 59 years old); it combined HIV care and community mobilization to improve IPV-related behaviors, decrease physical IPV, and decrease HIV incidence [19]. Another successful trial was IMAGE, which reduced IPV among older adolescents and adults in South Africa through a combination intervention incorporating gender issues and microfinance. The original IMAGE trial, however, did not include adolescents under 18 years of age and was conducted in a rural setting [20]. Amongst the age group that is the focus on this study, adolescents 10–14, there have been some promising studies in high-income countries, although most have had short follow-up periods and/or only query changes in skills, not actual assault. Examples include an empowerment self-defense based intervention in New Zealand [21] and a skills and knowledge program in California [22].

Our research group has also conducted preliminary studies of the interventions described in this paper. In 2012 and 2013, we evaluated similar girls’ empowerment and boys’ transformation interventions, separately, in secondary schools (student ages 13–20) in several Nairobi settlements. The intervention for girls was based on an empowerment self-defense approach or “resistance” approach, which has only been studied in high-income countries, [23–27] and almost always with positive results. The primary outcome in the girls’ studies was sexual assault incidence. The interventions were successful in significantly reducing incidence by 38–63% compared to the girls receiving the standard-of-care (SOC) [5, 28]. The boys’ intervention reduced negative gender norms; these changes were sustained one year later. It also increased the likelihood of boys intervening on behalf of girls in risky situations [29]. In 2014, we researched a pilot expansion of these stand-alone interventions into a dual-gender program, where boys and girls received complementary, parallel, but separate interventions. That expansion also involved randomization and enrolling a younger population, between 10 and 14 years of age (in upper primary school). In that study, we found the intervention caused a decrease of 3.7 percentage points in annual incidence of rape from a baseline of 7.3% [6]. The three early studies were all observational with convenience sampling, and the randomized trial was an open-cohort design without individual longitudinal follow-up. In addition, the maximum follow-up period in these studies was 10 months, with the ability to collect data on covariates limited due to resource constraints.

This study fills significant gaps in the knowledge base, specifically about adolescents in urban settlements. It is a replication study of our previous RCT, but also improves upon our previous study design by providing longitudinal follow-up, a longer follow-up period (24 months), the ability to collect covariates that may help predict or explain outcomes, and a revised intervention for boys that focuses on positive masculinity as well as gender norms. It was also the largest study ever of an empowerment/self-defense based approach for rape prevention among adolescents.

### Current study

This protocol tested the effectiveness of an intervention combining the successful girls’ intervention, IMPower, and a significantly revised boys’ intervention, Source of Strength (SOS). As these are challenging populations and environments, with very limited resources or infrastructure, and high levels of poverty and crime, they required innovative partnerships and methods in order to conduct a rigorous randomized-controlled trial. These approaches are described below.

## Methods/design

### Study design

This was a two-arm, parallel, cluster-randomized trial with clusters defined as schools within the settlements. Data collection began in January 2016 and continued through December 2018.

The study was conducted in six informal settlements in Nairobi: Kibera, Mukuru, Huruma, Dandora, Kariobangi, and Korogocho. For the purposes of the study, given the small number of schools from Kariobangi, Kariobangi schools were considered part of the Dandora settlement. Local partners included three non-governmental organizations, No Means No Worldwide (NMNW), Ujamaa Africa, and the African Institute for Health and Development (AIHD). NMNW created the intervention, Ujamaa implemented the intervention, and AIHD was the Nairobi-based research partner for the evaluation component of the study. Stanford University was the independent, external evaluator of the intervention.

The primary outcome was the change in incidence of self-reported sexual assault among adolescent girls from baseline, comparing the IMpower and SOS interventions to a SOC intervention. Secondary outcomes included determining the impact of the interventions on self-efficacy, self-esteem, gender attitudes and beliefs, and experiences of physical and emotional violence. We also measured episodes of perpetrating violence and bystander behaviors among adolescent boys. In follow-up surveys, we collected data on acceptability of the program and how often adolescents recall using specific skills from the program. All of these data were collected using quantitative surveys. We also collected process data at follow-up on what components of the intervention the adolescents found useful and what the adolescents suggest changing about the intervention in the future. Stakeholder meeting of teachers, head teachers, and officials from the Kenyan Ministry of Education were held before each round of data collection to answer questions and gain buy-in.

We also collected qualitative data through in-depth interviews with both girls and boys. These focused on the experiences and understanding of violence in the communities, as well as characteristics of implementation to gain a deeper understanding of successes and failures of the intervention.

### Inclusion/exclusion criteria

Included schools could be operated by the government, non-governmental organizations (NGOs), or private enterprises, but must not have received the intervention in the previous 3 years (the intervention has been previously taught in several of these communities). Participating schools must operate within, or draw most of their student population from, one of the informal settlements listed above. Due to the dynamic nature of school recruitment and deployment of the study, some schools withdrew post-randomization but pre-deployment. One school dropped out post-randomization, and it was replaced with a different school.

Inclusion/exclusion criteria for adolescents included: enrolled in class six (sixth grade) in a sampled school (see sampling description below), able to communicate in at least one of the study languages (English or Kiswahili), and not suffering from a significant mental deficit (learning difficulty, mental illness or substance abuse) that would impair their ability to consent to participation in the trial (as determined by school and study staff).

### Randomization

Clusters: Stanford researchers used pre-trial characteristics of the schools to create matched sets of schools. Matching before randomization was used to reduce discrepancies in important covariates values across arms of the trials arising during randomization [30]. The school-level covariates considered in the matching were the number of girls and boys (separated by sex) in classes 5–8 (separated by class), school-level average standardized test scores, number of toilets (by sex), teachers per capita, settlement, school sponsor type (i.e., government, private, religious), and physical building materials (wall material, roof material). Within each matched set, one school was assigned to the standard of care (SOC) arm and one school to the girls’ intervention (Table 1). Each school within the set had an equal probability of being assigned to either of the two arms. Randomizations resulting in any pairwise standardized difference outside of the range [− 0.1, 0.1] were rejected and the randomization was rerun. Due to logistics of deploying the intervention, three cohorts of schools were randomized. The cohorts had no intentional distinctions, other than when the schools were recruited. As the intervention is a training program, it is not possible to blind schools or trainers to their study arm.

**Table 1 Tab1:** Summary of randomization of the 108 schools randomized to treatment or SOC

Baseline covariate	Mean of Treatment Schools	Mean of SOC Schools	Pooled Standard Deviation	Standardized Mean Difference
Number of girls in class 6	78	74	56	0.08
Number of boys in class 6	72	73	55	−0.02
Total number of students in school	571	560	410	0.03
Total number of teachers in school	15	15	8	0.01
Teachers per capita schoolwide	53.2	49.9	42.1	0.08
Total number of rooms where classes are taught	11	9	5	0.25
School’s mean score on prior year’s standardized test	270	269	40	0.02
Missing indicator for prior year’s standardized test	6%	9%	25%	−0.12
Number of toilets per capita in school	0.05	0.04	0.03	0.08
Percent of schools in Dandora	24%	15%	40%	0.22
Percent of schools in Huruma	32%	18%	44%	0.33
Percent of schools in Kibera	15%	9%	34%	0.17
Percent of schools in Korogocho	12%	26%	39%	−0.38
Percent of schools funded by government	68%	59%	50%	0.18
Percent of schools funded privately	18%	24%	42%	−0.14
Percent of schools funded by religious institution	3%	9%	29%	−0.20
Percent of schools with walls made of stone	38%	50%	50%	−0.24
Percent of schools with walls made of blocks	18%	15%	37%	0.08
Percent of schools with walls made of tin sheets	9%	18%	34%	−0.26
Percent of schools with walls made of concrete	12%	9%	29%	0.10
Percent of schools with roof made of iron sheets	82%	79%	38%	0.08

Individuals: Among smaller schools (*n* < 40, within sex, in grade 6), all pupils in the school participated in the baseline survey. For logistical reasons, in large schools, adolescents were randomly selected using a lottery method (picking colored beads from an opaque bag) to participate in the surveys. The larger schools tended to be sampled to sizes less than 70 per sex.

### Sample size

We powered the study to distinguish the intervention from the SOC group based on the sexual assault prevention outcome. Based on our 2013–14 pilot study, we assumed that baseline annual incidence in similar informal settlements, in this age group, is 7.3% [6]. From this prior study, we also estimated the interclass correlation to be approximately 0.001.

We calculated sample size to achieve 80% power of detecting approximately a 40% decrease in the odds of sexual assault as reported by the participants when comparing the intervention group to SOC group (technically, calculated as a risk difference from 0.07 to 0.044). We took into account a school-level dropout of 25% and a participant-level dropout of 25% over the course of the study. Calculations to determine the sample size were run using the *CRTSize* package in R, function *n4props()* [31]. Given the above assumptions, we estimated that we needed a minimum of 45 schools for each arm of the trial, with at least 40 girls in each school.

We also recruited male participants into the study to complete surveys in order to better understand their experiences of violence in this setting. As this is an exploratory aim, this study is not powered on boys’ outcomes. The specific number of boys studied in each school was maximized given restrictions due to funding; we randomly sampled between 5 and 15 boys per school and included all of the sampled schools that had boys enrolled in class 6.

For the qualitative data, we purposively sampled 20 girls and ten boys from one participating school in the Dandora neighborhood to participate in in-depth interviews. This sampling approach was taken in order to allow for deep understanding of one of the study communities.

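### At a conventional two-sided 5% level, the stated minimum of 45 schools per arm with 40 girls each gives about 70% power after both dropout allowances, not 80%; alpha and sidedness are not stated

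*Protocol article*

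**What the plan says.** All the relevant statements but one are in the Sample size section of the protocol article.

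- Target: "We calculated sample size to achieve 80% power of detecting approximately a 40% decrease in the odds of sexual assault", with the rates given as "technically, calculated as a risk difference from 0.07 to 0.044".
- Source of the control rate: "we assumed that baseline annual incidence in similar informal settlements, in this age group, is 7.3" (per cent), taken from the pilot study.
- Clustering: "we also estimated the interclass correlation to be approximately 0.001".
- Attrition: "We took into account a school-level dropout of 25% and a participant-level dropout of 25% over the course of the study".
- Result: "we needed a minimum of 45 schools for each arm of the trial, with at least 40 girls in each school".

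The section names the R function used but not the arguments passed to it. No significance level or sidedness appears there or elsewhere in the article. The caption of Table 1, under Randomization, gives the number of schools as 108: "Summary of randomization of the 108 schools randomized to treatment or SOC".

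**The concern.** The section supplies every input to a standard cluster calculation except alpha, so the result can be checked. At the usual two-sided 5% level, the stated inputs with both 25% losses do not lead to 45 schools per arm. They lead to a number in the high fifties.

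This calculation is the stated basis for the trial's size on its primary outcome, and a reader will use the 80% when weighing a null result. If true power at the stated minimum is nearer 70%, the chance of missing the targeted effect is about 30% rather than 20%.

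**Working it through.** **Inputs from the article.** Rates 0.07 and 0.044; ICC 0.001; 40 girls per school; 25% of schools and 25% of girls lost; 80% power; equal allocation.

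**Assumption.** Alpha is not given. I take 5% two-sided as the main case and one-sided as the alternative.

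**Formulas.**
- Girls per arm without clustering: n = (z_alpha + z_beta)² × [p1(1−p1) + p2(1−p2)] / (p1−p2)²
- Design effect: DE = 1 + (m−1) × ICC, where m is girls analysed per school
- Schools per arm: k = n × DE / m, divided by 0.75 if schools are lost
- Participant loss takes m from 40 to 30

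**Schools needed, two-sided 5%, 0.07 v 0.044.** The variance term is 0.07×0.93 + 0.044×0.956 = 0.10716, so n = 7.849 × 0.10716 / 0.026² = 1,244.

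| Dropout allowed for | m | DE | Schools per arm (normal) | Schools per arm (t quantiles) |
|---|---|---|---|---|
| Schools only | 40 | 1.039 | 32.3/0.75 = 43.1 | 33.3/0.75 = 44.4 |
| Girls only | 30 | 1.029 | 42.7 | 43.7 |
| Both | 30 | 1.029 | 42.7/0.75 = 56.9 | 43.7/0.75 = 58.2 |

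One allowance therefore gives 43 to 45 schools after rounding up. Both give 57 to 59.

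**Power at the stated minimum after both losses.** 45 × 0.75 = 33.75 schools and 40 × 0.75 = 30 girls, so 1,012.5 girls per arm. Then z = 0.026 / √(0.10716 × 1.029 / 1,012.5) = 2.49.
- Two-sided 5%: Φ(2.49 − 1.96) = 70.2% (69% with a t reference).
- One-sided 5%: Φ(2.49 − 1.645) = 80.1%.

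**Reproducing the stated 45.** At one-sided 5%, n = 980, and 980 × 1.029 / 30 = 33.6; 33.6/0.75 = 44.8, so 45. This recovers the article's figures with both losses, using the normal formula and rounding only at the end. Rounding up at each step, or using t quantiles (45.9), gives 46.

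**Control rate 7.3%.** 0.073 × 0.6 = 0.0438, whereas 0.07 × 0.6 = 0.042, so 0.07 may be a rounded 7.3%. At two-sided 5% with both losses, power at the minimum is 78.4% (0.073 v 0.044) to 79.0% (0.073 v 0.0438) by the normal formula. For 80% power, 46.1 to 46.8 schools per arm are needed, so 47. At one-sided 5% the power is 86–87%.

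**Schools actually randomized.** 108/2 = 54 per arm if split equally; 54 × 0.75 = 40.5 schools of 30 girls. Two-sided power is 77.9% for 0.07 v 0.044, and 85–86% with 0.073.

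**Reading 45 × 40 as numbers left after dropout.** Two-sided power would be 91%, and 45/0.75 = 60 schools per arm would have to be randomized, against 54.

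**Sensitivity to the ICC.** At ICC 0.01, DE = 1.29 and power at the minimum is about 60% (two-sided, 0.07 v 0.044).

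**The case against.** The strongest reply is that two-sided 5% is the reader's assumption, not the plan's. At one-sided 5% the article's numbers fit together with both dropouts included. This stands: it cannot be said that no reading gives 45 schools, 40 girls, both losses and 80% power. But the article nowhere declares a one-sided test, and one would need declaring.

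A reader might also infer that the authors applied only one of the two allowances, because a single allowance gives 43 to 45 schools. The article does not show this. With the plain normal formula, neither single allowance gives 45 (44 and 43 after rounding up). The t-based route does give 45 for school loss alone, but the article does not describe the algorithm behind the named function. The closeness of the numbers is suggestive only.

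Third, the control rate may have been 7.3%, which reduces the shortfall to one or two points. That is possible, but the text says the calculation ran from 0.07. Even 0.073 gives neither 45 schools nor 80% at two-sided 5%.

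Last, 45 and 40 are minima and 108 schools were randomized. This also stands. At 54 schools per arm the gap is about two points with 0.07 and disappears with 0.073. More than 40 girls per school on average would narrow it further. The practical consequence is therefore modest.

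**Conclusion.** The claimed 80% does not follow from the stated inputs at the conventional two-sided 5% level. At the stated minimum, after both losses, power is about 70% with the stated rate of 0.07, and 57 to 59 schools per arm would be needed for 80%. If the control rate was 7.3%, power is 78–79%. With the stated 0.07, the 80% is met only under a one-sided 5% test that the text does not mention.

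These figures rest on an ICC of 0.001, exactly 40 girls enrolled per school, and losses applied as 25% of schools and then 25% of girls in the remaining schools. The finding is that the power statement is incomplete and, at the usual level, too high. It does not establish how the authors reached 45. Because the trial randomized more than the minimum, I rate it should-fix.

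**What to change.** In the Sample size section, state alpha and sidedness, the exact control rate used (0.07 or 0.073), and how each 25% dropout entered the calculation.

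Unless a one-sided 5% test was used, restate the power:
- at the stated minimum, about 70% (control rate 0.07) or 78–79% (0.073);
- at the 108 schools randomized (54 per arm if split equally, 40 girls each, both dropouts), about 78% (0.07) or 85–86% (0.073).

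If a one-sided 5% test was used, say so; the 80% can then stay. A sensitivity line for a higher ICC would help but is optional: about 60% at the stated minimum with ICC 0.01, two-sided, 0.07 v 0.044.

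The cost is a few sentences and possibly a less favourable power figure. No change to recruitment, design or analysis is asked for.
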